### Blood sampling

As per standard of care for patients with ARF within ICU, regular ABGs (approximately four to six per day) are collected via an arterial line to monitor several indices within the blood (such as PaO_2_, PaCO_2_, PF ratios, serum creatinine, and methaemoglobin (MetHb) levels). Further ABGs can also be requested by the medical treating team as clinically indicated. To monitor responses to therapy within the study, participants will have several ABGs completed at pre-determined timepoints (Fig. 1), most of which will occur as part of standard care within ICU. However, specific timepoints (such as six and 12 hours after study inclusion) may require additional ABGs. In these instances, approximately 4 ml of blood will be collected from participants via their arterial line for analysis within ICU. No further ABGs will be collected if/when an arterial line is removed, therefore, negating the requirement of an arterial stab.

### Intervention timing

Timing of interventions and assessments during the study will occur via the schedules outlined in Figs. 1 and 2.

### Outcome measurements

Primary outcome.Feasibility◦Recruitment (at least 75% of all eligible patients recruited using approved consent methods)◦Retention (at least 80% of consented pts remaining within study)◦Protocol fidelity (at least 70% of pts in intervention group receiving HFO_2_+iNO for at least 22 h a day (accounting for times where/if iNO is ceased (e.g. transport, investigations, mobility away from the bedspace))◦Data collection procedures (at least 90% of in-person data collected at each study time point)Clinical outcomes (specific timepoints in Fig. 2)Number of patients in each arm progressed to IMV within 28 daysMetHb levels measured via ABGsDaily serum creatinine and urine output levels to monitor renal function and/or renal impairmentChange in PaO_2_ relative to baselineChange in PF ratio relative to baselinePhysiological data◦Respiratory rate (RR)◦SpO_2_◦Systolic blood pressure (SBP)◦Heart rate (HR)Illness severity as estimated by daily sequential organ failure assessment (SOFA) scores [42]Worst daily PF ratioROX index scoresReason for intubation◦Respiratory failure◦Circulatory failure◦Neurological failure◦SurgeryParticipant experience survey (Appendix 1)ICU LOSHospital LOSMechanical ventilation hoursNumber of ventilator free days at day 28Time to mobilisation (minimum classification 4 (standing) on the ICU mobility scale) [43]Best mobility (within first 24 h and during whole length of stay)Daily delirium incidence (Confusion Assessment Method for the ICU (CAM-ICU) score)Retrospective pre-ICU EuroQol 5-Dimension 5-Level (EQ-5D-5L) questionnaireEQ-5D-5L (collected within 5–7 days of discharge from the ICU)Need for anxiolytic and sedative medication during admissionICU mortality

### Data collection

Eligibility and recruitment data will be gained from the electronic screening log. The screening log will be used to document all patients who have been screened and identify those who consented to enrol in the study and those who were not enrolled, remarking the specific reason for exclusion. Data in relation to demography, physiology, admission severity of illness, haemodynamic data, details of haemodynamic support, and hepatic and renal functions will be collected by local data managers from electronic medical records.

Safety data will be collected for each patient including (i) MetHb levels, (ii) daily serum creatinine and urine output levels to monitor renal function and/or renal impairment, and (iii) adverse and serious adverse events (see section "Data handling and record keeping" below for further details).

### Data handling and record keeping

Case Report Forms (CRF’s) will be collected initially in hard copy before being transferred to an electronic format which will be stored on a password protected Queensland Health server. Paper documents will be stored in a secured locked cabinet at the study site under the supervision of the principal investigator and study coordinator. An electronic copy of the data will be maintained via a password protected spreadsheet, and the principal investigator and study coordinator will be responsible for its management.

The study team will ensure all steps are taken to maintain confidentiality and security over the study documentation. Documents will be maintained for a minimum of 15 years following the completion of the study, as per Good Clinical Practice (GCP) guidelines.

### Safety considerations

#### Methaemoglobin levels across groups

Nitric oxide oxidises heme iron to the ferric state, resulting in the formation of MetHb [44]. Methaemoglobin has higher oxygen affinity and decreased oxygen-carrying capacity due to fewer hemes to bind oxygen [45]. Safe levels of MetHb within previous trials for iNO are considered < 5% [27]. Pooled data (1275 participants with ARDS receiving iNO) demonstrated MetHb levels > 5% for four participants in the iNO group and three participants in the control group [33]. Whilst this risk remains extremely low, MetHb levels will be monitored in all participants in this study via ABGs during the timepoints listed in Fig. 2.

#### Renal impairments across groups

Previous literature has demonstrated that iNO may induce renal impairment [33]. Depending on the definition, renal impairment in participants receiving iNO range from 5 to 13% [29, 46, 47]. However, of these results, only one study demonstrated a statistically significant increase in renal impairment in the intervention group when comparing to a control group of COT [47]. To further examine rates of renal impairment within this study, daily serum creatinine and urine output levels will be collected and compared across both groups. Renal impairment will be classified by the Acute Kidney Injury Network (AKIN) criteria [48] (Appendix 2).

#### Adverse and serious events

Any adverse event (AE) associated with the conduct of the study will be collected and reported to the study sponsor (Metro North Hospital and Health Service). Additionally, an annual safety report will be provided to the approving human research ethics committee in line with the local requirement at the study site.

The defined AEs for the trial are:Renal complications (including new haemofiltration/dialysis and/or acute kidney injury defined by the AKIN classification/staging system of acute kidney injury, Appendix 2)MetHb levels > 5%

Serious adverse events (SAEs):

The definition of a SAE is one that fulfills at least one of the following:Is fatal—results in deathIs life threateningRequires prolongation of existing hospitalisationResults in persistent or significant disability or incapacity [49]

Given that critically ill patients are likely to meet any of the above listed criteria during their ICU admission, only SAE’s that are thought to be related to the study will be reported. Serious adverse events will be reported to the study sponsor within 24 h of becoming aware of the event. For all events, a medically qualified study investigator will review the event and assign the causality relationship between the study intervention and the event (possibly, probably, or definitely related). Serious adverse events will also be periodically reviewed by an independent Data and Safety Monitoring Committee (DSMC). The DSMC consists of suitably qualified experts, including medical specialists and a biostatistician. There are no competing interests from the DSMC, and they remain independent from the study sponsor. A DSMC charter is kept within the study site file, only accessible to study personnel. Interim analysis of key efficacy and safety data will be undertaken by the DSMC when 50% of the projected total number of participants have been evaluated for the primary endpoint. The DSMC will meet after 25%, 50%, and 100% of the projected total number of participants have been recruited. After each meeting the DSMC will make one of several recommendations that may include continuing the study, proposing protocol changes, extending recruitment, or stopping the study early. If protocol changes are required, the trial registry will be updated accordingly, and study personnel will be notified and provided with the new protocol.

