## Introduction

Acute hypoxaemic respiratory failure is a common and life-threatening consequence of a diverse group of conditions [1, 2]. When conventional oxygen therapies (COT) (≤ 15 L/min oxygen via nasal prongs, cannula or mask) [3] or non-invasive ventilation (NIV) fail to correct hypoxaemia, invasive mechanical ventilation (IMV) is required. The use of IMV is common throughout the world and is increasing annually [4, 5]. Patients on IMV represent approximately 3% of acute hospitalisations and 30% of intensive care unit (ICU) admissions both internationally and in Australia [1, 2, 6–8]. However, outcomes of IMV are highly dependent on factors such as aetiology, age, co-morbidities, and severity of illness [9].

Whilst often a life-saving intervention, intubation and IMV are not without inherent risks. Risks include laryngeal injury, injury to lung parenchyma, adverse haemodynamic consequences (e.g. decreased venous return, blood pressure, and cardiac output) and predisposition to infection (e.g. ventilator-associated pneumonia (VAP)) [10–13]. Emergent endotracheal intubation also carries an especially high risk, with reported intubation-related cardiac arrest (occurring within 20 min after successful intubation) rates of up to 23% [14]. Despite evidence demonstrating a decrease in mortality rates over time, up to 30–40% of patients receiving IMV will not survive their ICU admission [15] and many survivors experience reduced quality of life, impaired physical function, and increased psychological conditions such as depression, anxiety and post-traumatic stress disorder [16, 17]. Invasive mechanical ventilation is also associated with significant increases in hospital and ICU length of stay (LOS) [6, 18], with increased cost burden ranging from 25 to 59% extra per ICU patient per day receiving IMV [7, 19, 20].

Reducing the incidence, risks, and costs associated with IMV is a major priority for healthcare providers, consumers, health system administrators, taxpayers, and policymakers [6]. By averting an artificial airway and IMV, patients with acute respiratory failure (ARF) supported with less invasive means can often avoid intravenous sedation and costly complications, such as VAP, ICU-acquired weakness, and line sepsis [6]. Avoiding intubation also facilitates patient-centric aims of early rehabilitation, speech, and oral feeding which may improve patient outcomes and reduce hospital and ICU LOS.

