## Aims

The primary aim of this pilot study is to examine the feasibility of comparing HFO_2_+iNO gas inhalation to HFO_2_ alone in patients with hypoxaemic, non-hypercapnic ARF. Several clinical outcomes (including safety and intubation rates) will also be examined. Based on the physiologic rationale [25, 37], prior investigations [28, 35, 36], and our anecdotal experience, we hypothesise that delivery of HFO_2_+iNO therapy is feasible, safe, and superior to HFO_2_ alone in preventing IMV in patients with ARF. This pilot study is a requisite initial step in exploring the proposed intervention [38] in preparation for a larger scale, multi-centre definitive trial. The feasibility and safety outcomes of the study protocol will inform future budget and protocol development whilst providing initial effect estimates to inform sample size calculation.

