### Inclusion and exclusion criteria

Patients will need to meet all inclusion criteria and no exclusion criteria (Table 1) to be eligible to participate.

**Table 1 Tab1:** Inclusion/exclusion criteria for review

Inclusion	Exclusion
• Age ≥ 18 years • Admitted to ICU • De novo type I respiratory failure (hypoxaemia in the absence of chronic lung condition) [24] • PF ratio < 300 mm Hg • High-flow nasal cannula determined by ICU medical team to be primary method for delivery of oxygen therapy • Anticipated HFO_2_ requirement > 24 h • Arterial line in-situ for blood gas sampling • Ability to provide informed consent, or consent via a SDM	• Congenital or acquired methaemoglobinaemia reductase deficiency • Bleeding diathesis • Intracranial haemorrhage • Severe left ventricular failure • Underlying chronic respiratory failure or exacerbation of asthma (including chronic obstructive pulmonary disease (COPD) or other chronic respiratory disease) • Documented cardiogenic pulmonary oedema or acute coronary syndrome • Hypercapnic respiratory failure with PaCO_2_ > 45 mm Hg • Deterioration of neurologic status demonstrated by Glasgow Coma Scale (GCS) ≤ 12 • Urgent need for intubation (evaluated by the medical officer in charge) • Haemodynamic instability (defined by systolic arterial blood pressure < 90 mm Hg or mean arterial blood pressure < 65 mm Hg) • Use of vasopressors • Do not intubate orders • Enrolled in any other trial of targeted oxygen therapy

*ICU* intensive care unit, *HFO*_*2*_ high-flow oxygen, *Hg* mercury, *mm* millimetres, *PaCO*_*2*_ partial pressure of arterial carbon dioxide, *PF* ratio of partial pressure of arterial oxygen to fraction of inspired oxygen, *SDM* substitute decision maker

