### Study interventions

Participants will receive one of two interventions: HFO_2_ alone or HFO_2_+iNO as detailed below.

High-flow oxygen (HFO2) alone (control group):

Initial FiO_2_ set at 100% with an initial flow of 60 L/minFiO_2_ will be titrated down in the first hour, targeting oxygen saturation (SpO_2_) > 92% and PaO_2_ > 60 mm HgFurther reduction in FiO_2_ every subsequent two hours maintaining SpO_2_ > 92% and PaO_2_ > 60 mm HgFlows will be reduced in increments of 10 L/min if needed for tolerance, to a minimum of 30 L/minHeated humidification to ensure delivery of HFO_2_ into the nares at a temperature set at 37 °C

High-flow oxygen and nitric oxide (HFO_2_+iNO) (intervention group):

High-flow oxygen therapy as described above, with the addition of:

iNO initially set at 20 parts per million (ppm) via HFNC by medical team, administered by ICU nursing staff, and weaned as per the following:◦After 24 h of study drug administration, wean iNO 1 ppm every 20 min or as directed by the treating ICU Consultant, provided:▪ PaO_2_ > 60 mm Hg and SpO_2_ > 92% for greater than 6 h with an FiO_2_ ≤ 50%FiO_2_ may be increased up to a maximum of 60% to compensate for any drop in oxygenation◦If nil decrement in oxygenation seen, iNO will be further weaned at a rate of 1 ppm/20 min to 0 ppm) or as directed by ICU Consultant◦If desaturation persists (SpO_2_ < 92%) for > 15 min, iNO will be returned to the most recent level prior to weaning or escalated up to a maximum of 20 ppm to maintain patient oxygenation◦iNO inhalation will be maintained if the patient in the HFO_2_ + iNO arm requires NIV

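### Apart from two defined adverse events, harms enter the safety record only if unblinded staff attribute them to the study, so the by-arm safety comparison is open to ascertainment bias

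*Protocol article*

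**What the plan says.** Three statements in the section Adverse and serious events govern what is recorded.

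- A general one: "Any adverse event (AE) associated with the conduct of the study will be collected and reported to the study sponsor".
- A list: "The defined AEs for the trial are:Renal complications (including new haemofiltration/dialysis and/or acute kidney injury" by the AKIN stages, and "MetHb levels > 5" per cent. These are the only adverse events given a definition.
- A serious-event rule. An event is serious if it is fatal, is life threatening, prolongs the hospital stay or leaves lasting disability. Because critically ill patients often meet these criteria anyway, only serious events thought related to the study are reported. An investigator assigns causality as possible, probable or definite. No unrelated category is listed.

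The Data collection section names adverse and serious adverse events as safety data beside methaemoglobin and renal measures. The Blinding section says that participants and treating clinicians know the allocation, and that participants are told both treatments are standard of care at the site.

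Elsewhere the article mentions other harms. The Introduction cites, for emergency intubation, "reported intubation-related cardiac arrest (occurring within 20 min after successful intubation) rates of up to 23" per cent. The weaning text under Study interventions provides for the case "If desaturation persists (SpO_2_ < 92%) for > 15 min". The fidelity target under Outcome measurements allows for nitric oxide being off: "accounting for times where/if iNO is ceased (e.g. transport, investigations, mobility away from the bedspace".

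The Aims section states: "we hypothesise that delivery of HFO_2_+iNO therapy is feasible, safe, and superior to HFO_2_ alone" in preventing invasive ventilation. It adds that the safety outcomes will inform the definitive protocol.

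**The concern.** For a comparison of harms between arms, events must be found and counted by the same rule in both. Only renal complications and raised methaemoglobin have such a rule here. Every other harm passes through a judgement: is it associated with the study, or related to it? That judgement is made by people who know the allocation. A bleed, an arrest or a desaturation in a patient on high-flow oxygen alone, described to participants as standard care, is unlikely to be called study-related. The same event on nitric oxide may be called related or put down to the underlying illness, depending on who judges. The by-arm count then reflects attribution as well as occurrence.

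The safety results of this pilot are meant to shape a larger trial. If they are lopsided, the definitive trial may choose the wrong safety endpoints or start from the wrong event rates. One question bears directly on the aim: does the added gas avoid intubation, or only postpone it to a more dangerous moment? An arrest soon after intubation would speak to that, and the article does not assure that it is counted alike in both arms.

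**Working it through.** No figure in the article states the size of this problem, so the check is mainly a reading of the sections against each other.

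**Step 1. How each harm would be captured.**

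| Harm | Where mentioned | Defined adverse event or outcome? | Route into the record |
|---|---|---|---|
| Renal complication | Safety considerations | Yes | Counted in both arms |
| Methaemoglobin above 5% | Safety considerations | Yes | Counted in both arms |
| Arrest within 20 min of intubation | Introduction | No | Serious event, if thought related |
| Sustained SpO2 below 92% when nitric oxide is reduced or ceased | Study interventions; Outcome measurements | No | Adverse event, if associated with study conduct; SpO2 also read at set times |

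**Step 2. What attribution does to a comparison.** Let n be the patients per arm, p the true risk, and a the probability that an event is attributed to the study. The expected recorded count is n × p × a. If p is equal in both arms, the ratio of recorded counts is a(nitric oxide) / a(control), so any difference in attribution appears as a difference in harm. With n = 20 (Sample size section) and an assumed p of 10%, 20 × 0.10 = 2 events are expected in each arm. At the extremes:

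- all attributed on nitric oxide and none on control: 2 against 0, a spurious harm;
- none attributed in either arm: 0 against 0, whatever the true difference.

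The bias can therefore run in either direction.

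**Step 3. Are such events likely enough to matter at this size?** The chance of at least one event in an arm is 1 − (1 − p)^20. The values of p are assumptions, since the article gives no rates for these events on nitric oxide.

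| p | Chance of at least one in 20 |
|---|---|
| 1% | 18% |
| 2% | 33% |
| 5% | 64% |
| 10% | 88% |

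This is the chance that an event occurs, not that it goes unrecorded. In the other direction, 0 of 20 recorded leaves an exact two-sided 95% upper limit of 1 − 0.025^(1/20) = 16.8% (one-sided, 1 − 0.05^(1/20) = 13.9%). One missed event changes the reading of such a table.

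**Step 4. A ceiling for arrest.** With the article's assumed intubation proportion, 0.38 × 20 = 7.6 intubations per arm, and 7.6 × 0.23 = 1.7 arrests. This applies a maximum cited for emergency intubation to every intubation, so it is an upper limit and not an estimate.

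**Step 5. Interruptions.** A fidelity day needs at least 22 h on nitric oxide, so it can contain up to 24 − 22 = 2 h off. The default wean from 20 ppm at 1 ppm per 20 min takes 20 × 20 = 400 min, unless the consultant directs otherwise. The article does not say how a cessation for transport relates to that text, and attaches no safety outcome to it.

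**The case against.** The strongest reply is that the article does collect other events. Its general sentence covers any adverse event associated with the study, and the Data collection section lists adverse and serious events separately from the two laboratory items. The two items may simply be those needing a formal definition, matching the two subsections on methaemoglobin and renal impairment. An arrest would be life threatening and, if thought related, would reach the sponsor within 24 h. An independent monitoring committee reviews serious events and sees safety data at the halfway analysis. Much is also recorded whatever the attribution: intubation by arm and its reason, SpO2, blood pressure, heart rate, PF ratio, ROX, SOFA, ICU mortality, and Kaplan-Meier curves for intubation or death.

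All of this stands, and it rules out a stronger reading. A reader might infer that the list is closed, that other harms go uncounted, and that the nitric oxide arm would look safe by construction. The documents do not support that. Nothing says that only two events are recorded, related serious events have a route, and no rule declares the arm safe; the stated success criterion is fidelity. Nor can it be said that the trial could not tell delayed from avoided intubation, since time to intubation, its reason and oxygenation give a partial view.

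A reader might also take "Bleeding diathesis • Intracranial haemorrhage • Severe left ventricular failure" among the exclusions as a list of anticipated harms of nitric oxide. Exclusion criteria alone do not show that, and no section says that the gas causes them. Finally, the weaning text and the fidelity allowance do not contradict each other: one governs weaning, the other scores time on treatment.

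The reply does not remove the dependence on attribution. The general sentence is itself limited to events associated with the study, and the committee's view of serious events may rest on what has passed the relatedness judgement. The other recorded outcomes are proxies: none identifies an arrest after intubation or a desaturation during an interruption. The assessment schedule, appendices, case report forms and full protocol are not shown and may say more, but the relatedness limit is stated in the article itself.

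**Conclusion.** The point holds as one of ambiguity and unequal ascertainment. The article does not say whether its two defined events are the whole list, and it makes the recording or reporting of other harms depend on judged relatedness, in an open-label trial and on a scale with no place for unrelated events. A fair by-arm count is thus not assured for harms that the article itself mentions.

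The size of the bias cannot be calculated, because it depends on attribution probabilities that no document gives. It matters because counts will be small: with 20 per arm, one or two events decide what the safety table appears to show. The conclusion assumes that control-arm events are less readily attributed to the study, which is plausible when that arm is presented as standard care but is not stated.

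This does not undermine the feasibility aims. It limits what the pilot can say about safety, and it can be corrected cheaply.

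**What to change.** In Adverse and serious events:

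1. State that renal complications and methaemoglobin above 5% are events of special interest and not the whole list.
2. Keep expedited reporting to the sponsor limited to related serious events, but record all serious events and tabulate them by arm irrespective of relatedness. Add an unrelated category to the causality scale.
3. Record a few objectively defined events in both arms, whatever their attribution, using definitions already in the article: cardiac arrest within 20 min of intubation (Introduction); SpO2 below 92% for more than 15 min (Study interventions), flagged when it falls in a nitric oxide wean or interruption; systolic pressure below 90 or mean pressure below 65 mm Hg, or start of a vasopressor (Table 1). Clinically significant bleeding could be an optional item. These are recording definitions, not treatment rules.
4. Log each nitric oxide interruption with its start, end and reason, and clarify how the cessations allowed for in the fidelity outcome relate to the weaning text. The clinical content is for the investigators to settle.

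The cost is a few more case report form fields, largely from bedside data already reviewed, and a safety table that looks less clean. The Trial status section says recruitment had not begun at the time of writing but was planned for June 2025. If it has since begun, an amendment is needed, with back-completion from records for patients already enrolled.

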### Sample size

As a pilot trial, it is not required to be powered to detect statistical significance. A sample of 40 eligible patients will be recruited over a period of 12–18 months. Assuming the proportion of patients who progress to IMV is 0.38 [24], a sample of 20 per group will produce an exact 95% CI width of 0.44.

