## Limitations

This single-centre, pilot study will sample 40 patients. As a pilot study, it is not powered to detect statistically significant differences in primary and/or secondary outcomes between groups. The ICU undertaking the study specialises in cardiothoracic medicine and surgery. Therefore, the results of the study may not be generalisable to other patient cohorts. With several consecutive timepoints allocated for blood collections to assess oxygenation and safety measures (Fig. 2), adherence in obtaining these measures may fluctuate, dependent on patient acuity. Finally, obtaining participant experience surveys may at times prove difficult, depending on factors like delirium and the level of respiratory distress a patient experiences at this timepoint.

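### The 20-patient interim has a trigger that does not fit the feasibility primary outcome and an efficacy content it cannot support, and the serious events reported are filtered by open-label relatedness

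*Protocol article*

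**What the plan says.** Under Adverse and serious events, the protocol article plans one interim analysis: "Interim analysis of key efficacy and safety data will be undertaken by the DSMC when 50% of the projected total number of participants". The condition set for those patients is that they "have been evaluated for the primary endpoint". The sentence after it sets the committee's calendar on a different clock: "The DSMC will meet after 25%, 50%, and 100% of the projected total number of participants have been recruited". After each meeting the DSMC may, among other things, advise continuing, changing the protocol, prolonging recruitment or ending the study early.

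Outcome measurements makes feasibility primary, with four components: recruitment, retention, protocol fidelity and data collection. IMV within 28 days heads the separate list of clinical outcomes.

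The Limitations section says of the whole trial that "it is not powered to detect statistically significant differences in primary and/or secondary outcomes between groups", and Statistical analysis declines detailed inference.

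On serious adverse events (SAEs), the article reports only those "that are thought to be related to the study will be reported", because critically ill patients often meet the seriousness criteria anyway. A medically qualified study investigator grades causality for all events as "possibly, probably, or definitely related". The trial is open label.

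**The concern.** Three things do not fit together.

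- **Trigger.** The interim waits for evaluation of a primary endpoint, but the plan has no single endpoint on which each participant is evaluated. The phrase would suit a 28-day efficacy endpoint, which this pilot does not have as primary.
- **Content.** The plan holds that 40 patients cannot support between-group inference, yet schedules an efficacy look at half that number without saying what the look is for.
- **Serious events.** Whether an SAE is reported depends on the judgement of an investigator who can know the allocation, and the scale has no place to record a judgement of no relation. A count of reported SAEs by arm therefore mixes event rates with attribution.

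At stake are the pilot's products: its feasibility estimates and the initial effect estimates meant to inform the definitive trial. A decision prompted by noise at 20 patients would damage both. On safety, an excess of serious events put down to the underlying illness would not show among the reported SAEs.

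**Working it through.** **Inputs.** Total 40, 20 per group, and IMV proportion 0.38 (Sample size); interim fraction 50% (Adverse and serious events); simple 1:1 allocation (Recruitment and consent).

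**1. The plan's own figure.** The article gives an exact 95% interval width of 0.44 for a proportion of 0.38 with 20 patients. Clopper-Pearson gives 0.154 to 0.592 for 7/20 (width 0.438) and 0.191 to 0.639 for 8/20 (width 0.448). The stated figure is reproduced.

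**2. Size of the interim.** 0.50 × 40 = 20 patients, or 10 per arm if the split is even. Simple randomisation does not guarantee that: a split of 7/13 or more uneven has probability about 0.26. Ten per arm is the favourable case.

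**3. Precision at the interim.** In one arm the exact 95% width is 0.59 at 3/10 and 0.62 at 4/10. For the difference between arms, with 0.38 in both, the half-width is

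1.96 × √(2 × 0.38 × 0.62 / 10) = 0.425.

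At the full 20 per arm the same formula gives 0.301, and the article already regards that sample as insufficient.

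**4. Chance differences.** Exact binomial, 10 per arm, 0.38 in both arms:

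- inhaled nitric oxide (iNO) appears at least 20 points better: probability 0.245
- iNO appears at least 30 points better: probability 0.124

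If the truth were 0.38 against 0.25 (the 0.25 is an assumption), the iNO arm would show an equal or higher IMV proportion with probability 0.346.

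**5. Power at the interim.** Two-sided 0.05, 10 per arm, 0.38 against an assumed IMV proportion with iNO:

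| Assumed proportion with iNO | Fisher exact | Normal approximation |
|---|---|---|
| 0.28 | 2% | 7% |
| 0.19 | 5% | 15% |
| 0.10 | 13% | 30% |

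**6. Trigger against primary outcome.**

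- Recruitment ("Recruitment (at least 75% of all eligible patients recruited using approved consent methods") has eligible patients as its denominator, so a participant cannot be evaluated for it.
- Data collection is a rate at each study time point.
- Fidelity is defined in the intervention group only, about 10 of the first 20 patients.
- Retention can be scored per participant, as can fidelity within its arm. The mismatch is substantial but not total.

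**7. Trigger against meeting.** If 28-day IMV is what was meant, the 20th patient is evaluated up to 28 days after being recruited. A meeting called at the 20th recruit would then see incomplete interim data.

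**8. Serious events.** Reporting requires a judgement that the event is related. The scale applied to all events starts at possibly related. An SAE judged unrelated thus has no recorded category and is not reported.

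**The case against.** The strongest reply is that the article states no efficacy stopping rule. The possible recommendations are a general list that applies after each meeting; extension could follow from slow recruitment and stopping from a safety signal. A DSMC charter exists but is not shown, and the committee includes a biostatistician. With 38% in both arms, a two-sided Fisher test at 10 per arm would reach 0.05 in only about 1.3% of trials. This stands. A reader might infer that the pilot will be stopped or extended on efficacy; the document does not say so. Nothing shown rules it out either, and the purpose of the efficacy content is left open.

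Second, a reader might infer that the DSMC has no unfiltered safety comparison. That is not shown. Methaemoglobin (MetHb), creatinine and urine output are collected for every patient, renal measures are to be compared across groups, and ICU mortality is an outcome. These may reach the committee as key safety data; the article does not say whether they do. The relatedness filter applies to SAEs and has a stated reason.

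Third, it is tempting to say that related SAEs will come almost only from the iNO arm. The text does not support this: the criterion is relation to the study, and high-flow oxygen alone is also listed as a study intervention.

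Fourth, two triggers in separate sentences are not in themselves a contradiction, since the article never says that the interim is presented at the 50% meeting. That is fair. The difficulty arises only if 28-day IMV is the intended endpoint, and the wording does not settle that.

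**Conclusion.** The concern holds in limited form, as a change that should be made. The interim trigger refers to a primary endpoint that does not match the four-part feasibility outcome. The efficacy content cannot inform a decision: the half-width is about 43 points at 10 per arm, and power to see a halving of 0.38 is about 5% (Fisher) to 15% (normal approximation). The reported SAEs do not give a comparison between arms that is free of attribution, and the causality scale is incomplete for the events to which it is applied.

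The figures rest on the protocol's 38% and an even split; the proportions with iNO are assumptions. It is not claimed that an efficacy stop is planned, that the DSMC certainly lacks unfiltered data, or that a missing boundary is an error, since the charter may cover it.

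**What to change.** 1. Define the interim as a review of safety and feasibility with one stated trigger: either the 20th patient recruited, or a stated follow-up point for those 20. Align the 50% meeting with it.
2. Add a sentence: *No stopping or extension of the trial will be based on efficacy.*
3. Give the DSMC counts by arm, regardless of attribution, of deaths, Acute Kidney Injury Network (AKIN) stage or new dialysis, and MetHb above 5%. Show IMV in that table as a safety event only, so that the noisy efficacy comparison does not return through the safety report.
4. Add *unlikely* and *not related* to the causality scale. The existing reporting of related SAEs to the sponsor can stay as it is.

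The cost is minor wording in the protocol and charter and one extra by-arm table, mostly from data already collected. No patients or procedures are added. The article says recruitment had not started at the time of writing; if it has since, the change is still administrative.
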